### Sub‐study 2. Administering validated questionnaires and the novel questionnaire to parents across Level 1 countries

3.3

This sub‐study will explore the psychosocial impact of T1D screening outcome through questionnaires. Three established validated questionnaires and the novel questionnaire developed in sub‐study 1 will be used. All Level 1 countries will participate. Psychosocial impact is defined through general quality of life, anxiety and depression, and diabetes‐specific concerns and stress.

#### Participants (2)

3.3.1

Parents of children from ‘Level 1’ countries who participated in the screening programme will be invited into this sub‐study. Inclusion criteria are mother, father, parent and guardians 18 years and older, who are willing and able to provide written informed consent. All eligible families form the general population will be invited to complete the questionnaires. We invite both parents in the family to take part in questionnaires. However, we have no control over who (in what family role) will be answering and will register responses of both parents, one parent or guardians. We expect that the main decision‐maker or family caregiver will be likely to respond. Demographic variables such as parents' age, family role, marital status, educational level, occupational status will be collected and whenever possible, we will involve underserved families (those who come from socioeconomically disadvantaged or ethnically minoritised background). It is less feasible to identify those for the questionnaires, but all possible effort will be made to involve the underserved families into acceptability interviews.

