The balance of benefits and risks of population screening has drawn recent attention. Clinical outcomes were most often evidenced with drastic (5–10 times) reduced risk of diabetic ketoacidosis (DKA) at clinical manifestation of the disease for screened children.^7^ From the parents' perspective, some psychological trade‐offs were registered and some of these were related to anxiety and depressive symptoms. In ASK, DiPiS, GPPAD and Fr1da, identifying a child with islet‐specific Aab was associated with higher anxiety compared to having an Aab‐negative child, particularly in mothers. Following screening results notification, the German Fr1da study reported significantly increased median PHQ‐9 score in mothers of children with presymptomatic T1D compared to negative controls.^6^ Similarly, in the US‐based ASK study, anxiety level (SAI) in parents of autoantibody‐positive children rose following screening: 74% experienced SAI above clinical threshold at first follow‐up visit.^14^ Furthermore, anxiety arising from waiting for the onset of symptomatic T1D requiring insulin may lead to overly protective behaviours in parents.^4^, ^6^ In a newborn genetic testing study, increased maternal worry was found if the mother herself had type 1 diabetes.^15^

Conversely, psychosocial benefits relate to families of being aware of future diabetes risk. The TEDDY study, an international surveillance T1D program for genetically predisposed children, established that parents (*n* = 54) who knew of their child's positive Aab status demonstrated a decrease in stress in the first year post‐diagnosis and improved quality of life compared to those (*n* = 54) diagnosed in the community.^16^ This suggests a trend towards waning anxiety with time and possibly related to monitoring and support. However, in ASK, at visit 2–6 months after results notification, despite a significant decrease, 69% of parents reported clinically relevant anxiety.^14^

In terms of uptake, in TEDDY, enrolment was high for first degree relatives (65%) but lower from the general population (39%).^17^ Parents' satisfaction was high.^18^, ^19^, ^20^ Parents perceived benefits to outweigh harms^5^, ^21^ and twelve years after screening, parents perceived no adverse effects.^18^ With regards to (dis)continuation, adherence with the monitoring protocol in TEDDY was high at 62%, with large differences across countries,^22^ while in the longitudinal ABIS study, participation was lower at 43.8% at 5–6 years.^23^

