#### Data analysis (2)

3.3.3

Exploratory data analyses and graphical representations of the data will be used to check validity. The study design includes repeated measures on all outcomes; thus, linear mixed‐effect models that correspond well to this structure (e.g. Linear Mixed Models in SPSS) will be used to analyse the data. Subgroup analyses are planned by sex and age (of parents/participant); the main result will be the analyses of the pooled data and a secondary country‐specific analysis (i.e., paired and non‐paired).

Due to the intrinsic nature of the observational study (and not a clinical trial), a randomisation process is not foreseen. However, we are fully aware of the importance of constructing a sample that is representative of the general population. For this reason, we will employ statistical tools capable of addressing potential biases arising from the lack of randomisation. Specifically, multivariate models will be implemented to account for possible confounding variables, such as education level. In addition, a stratified analysis will be conducted, dividing the study population into homogeneous subgroups (strata) based on one or more confounding variables (e.g., age, education level). A dedicated missing data analysis will be conducted to address this issue. Sensitivity analyses will be performed to assess both Missing at Random (MAR) and Informative (Non‐Random) Missingness. Missing data will be evaluated at specific time points as well as longitudinally over time, in order to determine whether dropout has occurred, resulting in loss to follow‐up.

The team identified SAI‐6 as the primary measure, assessing the psychological impact at different time points. The main hypotheses are: (1) in negative families, reduced parents' stress at T2 compared with T1; (2) in positive/presymptomatic families, reduced parents' stress at T4 compared with T2. Additional hypotheses will also be tested. Where patients progress rapidly to insulin after T2, they will only have T2 and T5 responses, but we feel this will be adequate as they would have participated in education. Information on symptom recognition will be given to all participants at the time of education.

The study will be reported according to Consort guidelines.

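### Sub-study 2 takes answers from either or both parents, but its mixed model names neither a family level nor the repeated unit, so within-family correlation and changes of respondent may enter the pooled time effect

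*Protocol article*

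**What the plan says.** Section 3.3.1 (Participants, sub-study 2) states: "We invite both parents in the family to take part in questionnaires". It continues: "However, we have no control over who (in what family role) will be answering and will register responses of both parents", or of one parent or a guardian. The main decision-maker or caregiver "will be likely to respond", which is an expectation and not a rule. Role is recorded: "family role, marital status, educational level, occupational status will be collected".

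Section 3.3.3 (Data analysis, sub-study 2) gives one reason for linear mixed models: "The study design includes repeated measures on all outcomes". On adjustment it says that "multivariate models will be implemented to account for possible confounding variables, such as education level". It plans subgroups by sex and age of the parent and makes the pooled analysis the main result. The country analysis mentions paired and non-paired comparisons, but the pair is not defined.

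The two main hypotheses, on SAI-6, concern parents' stress: lower at T2 than T1 in negative families, and lower at T4 than T2 in positive families. The Background reports that a positive antibody result was associated with more anxiety than having a negative "child, particularly in mothers". The Discussion gives a 10% significance level.

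**The concern.** Accepting both parents creates a level, the family, that the reason given for the model does not cover. Having no control over the respondent means that the person answering at T2 or T4 need not be the one who answered before. Two consequences follow, and their size depends on a unit that section 3.3.3 does not fix.

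- **Clustering.** Two parents live through the same screening result, so their changes in stress are likely to be correlated. If they count as independent, the standard error of the pooled change is too small.
- **Change of respondent.** If mothers and fathers score differently and the mix of respondents shifts between timepoints, part of that difference appears as change over time. Both main hypotheses are about change over time.

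The second consequence is partly a matter of data collection. If later questionnaires are not tied to a particular parent, analysis cannot fully recover the link.

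**Working it through.** The article gives no sample size, SD, partner correlation or share of two-parent families for sub-study 2, so there is no figure of its own to reproduce. From the document come the 10% level (taken as two-sided, since sidedness is not stated), the invitation to both parents and the contrasts T1-T2 and T2-T4. All other inputs below are assumptions, shown as ranges.

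**1. Two parents treated as independent.** Let f be the share of families with two respondents and ρ the correlation between partners in the quantity tested, here the change.

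Design effect: DE = [(1 − f) + f(2 + 2ρ)] / (1 + f)

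True size of a nominal 10% test: 2[1 − Φ(1.645/√DE)]

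| f | ρ = 0.3 | ρ = 0.5 |
|---|---|---|
| 25% | DE 1.12, size 12.0% | DE 1.20, size 13.3% |
| 50% | DE 1.20, size 13.3% | DE 1.33, size 15.4% |
| 100% | DE 1.30, size 14.9% | DE 1.50, size 17.9% |

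At ρ = 0.1 the sizes are 10.7%, 11.1% and 11.7%.

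**2. Change of respondent, records linked by family.** Let s be the net share of families moving from mother to father and d the mother-father difference in SD of the score. With no true change, the apparent change is −s × d.

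- s = 10%: 0.1 × 0.2 = 0.02 to 0.1 × 0.4 = 0.04 SD.
- s = 30%: 0.3 × 0.2 = 0.06 to 0.3 × 0.4 = 0.12 SD.

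A simulation with true change 0 and d = 0.3 gave −0.032, −0.059 and −0.087 SD at 10, 20 and 30% switching, against −0.03, −0.06 and −0.09 from the formula. Restricted to pairs from the same parent, it gave −0.001 to 0.004 SD.

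**3. Change of respondent, records linked by parent, role not in the model.** A mixed model also uses parents seen only once, so a mother seen only at T1 and a father seen only at T2 both inform the time effect. With within-parent correlation r, the weight on these single records is w = s / [s + (1 − s)/(1 − r)], and the apparent change is −w × d. Taking r = 0.6:

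- s = 10%: w = 0.1/(0.1 + 0.9/0.4) = 0.1/2.35 = 0.043, so the fall is 0.009 SD (d = 0.2) to 0.017 SD (d = 0.4).
- s = 30%: w = 0.3/(0.3 + 0.7/0.4) = 0.3/2.05 = 0.146, so the fall is 0.029 to 0.059 SD.

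This is 43-49% of the family-linked shift. A fixed effect for role removes it.

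**4. Direction.** Steps 2 and 3 give a fall only if net switching runs from mother to father and mothers score higher. Balanced switching gives zero, and net switching from father to mother would mask a true fall.

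**The case against.** The strongest reply is that the text points to the parent as the unit. Eligibility and consent are individual, and the subgroups are by the participant's own sex and age. The wording about negative and positive families can be read as naming the result group. On that reading, a change of respondent would be missing data for each parent and not a change score. The first part is fair and makes the full family-linked shift the less likely case. The second does not hold: step 3 shows that single-occasion records still feed the time effect unless role is modelled.

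Several limits stand:

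- The article does not say that respondents change between timepoints. That is inferred from the lack of control over who answers, and the expected main caregiver may be fairly stable.
- No reason is given to expect net drift from mothers to fathers.
- The Background's maternal finding concerns a positive result. It bears mainly on the second hypothesis and shows no role difference in negative families.
- Role is recorded, parent-sex subgroups are planned, education is only an example of a confounder, and a mixed model can hold a family effect. The full analysis plan, not shown, may include one. Subgroups, however, leave the pooled main result unprotected.

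A reader might infer that both problems apply at full strength together. The documents do not support this, because the repeated unit is not stated. With the family as unit, partners share the family effect and are not simply independent. With the parent as unit, the switching shift is only about half.

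**Conclusion.** The point holds in a limited form. The design creates two-respondent families and leaves the respondent uncontrolled, while the stated reason for the model covers repeated measures only. Followed as written, the main pooled analysis may ignore within-family correlation and leave respondent role in the time effect.

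The size is modest to moderate and rests on assumed inputs. True test size is about 12-15% against a nominal 10% when 25-50% of families give two respondents with ρ of 0.3-0.5. The 15-18% range requires every family to do so, which should not be read as the expected case. The switching shift is 0.02-0.12 SD if linked by family, 0.009-0.059 SD if linked by parent, and zero if switches balance.

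It would also go too far to conclude that the plan builds in a spurious fall favouring its hypotheses. The documents give neither the direction of switching nor the size of any role difference, and without a sample size one cannot say whether such a shift would reach significance. The change should be made because it is cheap and because linkage by parent is hard to restore after collection.

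**What to change.** - Give each parent an identifier linked to a family identifier, and address later questionnaires to the parent or parents who answered before.
- State that the parent is the repeated unit. Fit the mixed model with parent nested in family (family random intercept), and with family role and role-by-time as fixed effects. State the mix of roles over which the pooled change is averaged.
- Because the hypotheses concern changes, also allow partners' changes to correlate, through a family-by-occasion term or standard errors clustered on family. In a within-parent change a family intercept cancels out, so alone it would not correct the sizes in step 1. Nor does it remove the switching shift; the role term does that.
- Add two sensitivity analyses: changes within the same respondent only, and one parent per family.

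The cost is one extra identifier field, a few model terms and slightly wider intervals. The same-respondent and one-parent analyses use fewer records and will be less precise, which is acceptable for a sensitivity analysis.

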#### Data collection (2)

3.3.2

Four validated measures will be administered either online or paper copies via participating sites in the EDENT1FI study, followed by up to two reminders 1 week apart. The willingness of parents to complete the questionnaires is a well‐known and understandable problem. We try to counter this by providing motivating information and keeping the number of questionnaires to a minimum.

Validated measures: EQ‐5D‐5L [EQ‐5D‐5L | EuroQol]^26^ assesses quality of life self‐reported as of ‘today’; HADS—Hospital Anxiety and Depression Scale—14 items^27^ identifies cases (possible and probable) of anxiety disorders and depression among patients in nonpsychiatric hospital clinics; SAI‐6—State Anxiety Inventory 6 items^28^ is a short form of 20‐item STAI adapted for assessing stress in parents of at risk of developing diabetes children; Novel questionnaire (from sub‐study 1) following validation.

It is expected that following administration of the questionnaires, a HADS‐based risk decision tree will be used to elicit parents who have high scores of anxiety and/or depression, according to the HADS questionnaire. These individuals (expected in rare cases) will be promptly referred to psychological or medical professionals for the provision of psychotherapeutic support. Refusals to respond, withdrawals and missing data will be accurately documented. Monitoring of positive result families and associated education, including parents and siblings, is part of the ‘Monitoring’ Work Package and is being published elsewhere.

#### Data analysis (2)

3.3.3

Exploratory data analyses and graphical representations of the data will be used to check validity. The study design includes repeated measures on all outcomes; thus, linear mixed‐effect models that correspond well to this structure (e.g. Linear Mixed Models in SPSS) will be used to analyse the data. Subgroup analyses are planned by sex and age (of parents/participant); the main result will be the analyses of the pooled data and a secondary country‐specific analysis (i.e., paired and non‐paired).

Due to the intrinsic nature of the observational study (and not a clinical trial), a randomisation process is not foreseen. However, we are fully aware of the importance of constructing a sample that is representative of the general population. For this reason, we will employ statistical tools capable of addressing potential biases arising from the lack of randomisation. Specifically, multivariate models will be implemented to account for possible confounding variables, such as education level. In addition, a stratified analysis will be conducted, dividing the study population into homogeneous subgroups (strata) based on one or more confounding variables (e.g., age, education level). A dedicated missing data analysis will be conducted to address this issue. Sensitivity analyses will be performed to assess both Missing at Random (MAR) and Informative (Non‐Random) Missingness. Missing data will be evaluated at specific time points as well as longitudinally over time, in order to determine whether dropout has occurred, resulting in loss to follow‐up.

The team identified SAI‐6 as the primary measure, assessing the psychological impact at different time points. The main hypotheses are: (1) in negative families, reduced parents' stress at T2 compared with T1; (2) in positive/presymptomatic families, reduced parents' stress at T4 compared with T2. Additional hypotheses will also be tested. Where patients progress rapidly to insulin after T2, they will only have T2 and T5 responses, but we feel this will be adequate as they would have participated in education. Information on symptom recognition will be given to all participants at the time of education.

The study will be reported according to Consort guidelines.

### Sub‐study 3. Semi‐structured interviews with parents of children who have undergone or declined screening in Level 1 countries

3.4

This sub‐study will explore the acceptability of T1D screening outcome through qualitative interviews undertaken at specific timepoints in the screening and follow‐up pathway. All Level 1 countries will participate. Acceptability will be based on qualitative self‐reports, rather than on objective measures of drop‐out/attrition rates due to the variable modes of screening and testing across the participating centres. To achieve this, we conduct qualitative semi‐structured interviews with parents. We based our approach on the combined definition of acceptability agreed upon and adopted in our previous publication (i.e., systematic review accepted by Diabetologia). It should read: acceptability in Theoretical Framework of Acceptability is understood as a multi‐faceted construct that reflects the extent to which people delivering or receiving a healthcare intervention consider it to be appropriate, based on anticipated or experiential cognitive and emotional responses to the intervention.^29^ This framework consists of seven constructs related to acceptability including affective attitude, burden, perceived effectiveness, ethicality, intervention coherence, opportunity costs and self‐efficacy. Additional to psychological interpretation of acceptability, we will also extend our approach to include physical and social/interactional experiences, as informed by COM‐B (Capability, Opportunity and Motivation = Behaviour model^30^).

#### Participants (3)

3.4.1

Parents who have either taken part in the screening programme or declined will be recruited from Level 1 countries. They should be able to understand the consenting procedures and aims of the research. A broad range of parents will be invited for interviews, including those from minority ethnic and socioeconomically deprived groups.

We will invite two cohorts of parents: (1) those whose children took part in screening and received either positive (*n* = 10) or negative (*n* = 10) result—20 parents per country (*n* = 80); (2) those who declined their children's participation in screening for any reason,10 parents per country (*n* = 40). We estimate that these numbers will be sufficient to achieve thematic saturation. Withdrawn families are often challenging to reach. Reasons may be logistical, procedural and due to low acceptability—‘any reasons’ accounts for them all, but we will distinguish those in the process of analysis. Local centres will be recruiting decliners via community and paediatricians.

#### Data collection (3)

3.4.2

The semi‐structured interviews will be carried out via online platforms with video recording being switched off, via telephone or face‐to‐face. The timeframe for interviews is defined as 3 months following receipt of screening result or decline. Interviews will last 40–60 min and will be driven by an interview topic guide. Parents' interviews will include one to two interviews (with either/or both mother and father) per family and their comments on the children's experiences and opinions will be elicited too. Those parents whose child tested positively and progressing to insulin‐requiring T1D will also be interviewed post‐diagnosis.

We understand that the qualitative interviews with parents of children identified as high risk may cause some distress, and parents can choose to take a break or stop the interview at any time.

#### Data analysis (3)

3.4.3

Interviews will be audio‐recorded, transcribed, translated into English and analysed by the respective Level 1 countries. The data will be thematically analysed using the Braun and Clarke approach^31^ and informed by the combination of TFA and COM‐B theories.

### Sub‐study 4. Qualitative interviews with professional stakeholders in Level 1, 2 and 3 countries

3.5

This sub‐study will explore the acceptability and implementation of screening with professional stakeholders through structured interviews. The interviews will be focussed on the views around barriers and facilitators and will be tailored to innovation, context and feasibility of implementation.

#### Participants (4)

3.5.1

Healthcare professionals (HCPs), such as paediatricians, primary care practitioners and community‐based professional stakeholders, stakeholders—policy makers involved in planning and implementing the screening programme, as well as those who were not involved, will be approached. Purposive sampling will be used to select professional stakeholders to interview. The sample consists of 20 stakeholders from each country (*n* = 10 of those involved and *n* = 10 of those not involved in screening). Informed consent will be obtained from stakeholders prior to participation.

#### Data collection (4)

3.5.2

The structured interviews (all participating countries) will be carried out via telephone or online platforms as outlined in sub‐study 2 and be informed by the Consolidated Framework for Implementation Research (CFIR).^32^ The ‘final workshop’ conducted online will aim to synthesise learning and will last 90 min. During the workshop, key professional stakeholders, researchers and decision‐makers will discuss the results of both the parents' psychological impact and acceptability of the study, share common practices, identify the country‐specific differences and deliberate on further actions. The format of the first half of the workshop will be based on SWOT (Strengths, Weaknesses, Opportunities and Threats) analysis and the second part will focus on discussion of recommendations for the implementation of future screening programs.

